## Abstract

**Abstract:**

**Introduction:**

The WHO’s Integrated Management of Childhood Illness (IMCI) in young infants <2 months of age includes the identification and management of signs of possible serious bacterial infection (PSBI). However, equal importance is given to all the PSBI signs, which signal the need for referral and hospital management, except for fast breathing in infants aged 7–59 days, for which outpatient treatment by clinical staff working at a health facility is recommended. Moreover, studies to validate the importance of clinical signs of PSBI have mostly used the need for hospitalisation as the outcome. There is a need to further examine the association of signs of PSBI individually and in combination with risk of mortality and to analyse global data to inform global recommendations.

**Methods and analysis:**

We will create a dataset that integrates data from population-based studies globally with similar designs that have examined the presence of signs of PSBI identified by frontline health workers throughout the young infant period (days 0 to <60) and that have also recorded infant vital status. We will conduct pooled, individual-level analyses of the frequency of identification of signs individually and in combinations and will conduct three types of analyses of association of signs of PSBI with mortality: (1) case fatality, which has been used in a multisite study of mortality risk associated with signs of PSBI in young infants in Africa; (2) Cox regression, which will enable time-varying analysis of exposure in relation to mortality, as has been done in a multisite study in Asia and (3) machine learning analysis, which has not previously been applied to any of the available data.

**Ethics and dissemination:**

All prior studies incorporated into our pooled analysis were approved by the independent local ethics committee/institutional review board (IRB) at each study site in each country, and all study participants provided informed consent. This project was approved by the Stanford University School of Medicine IRB protocol 74456. Study findings will be disseminated through publications in peer-reviewed journals, WHO documents, and presentations at maternal and child health meetings.

STRENGTHS AND LIMITATIONS OF THIS STUDYPooling of individual subject data available globally.Pooling of population-based studies using common designs for subject enrolment, baseline covariates and assessment of community health worker (CHW)-identified clinical signs of the WHO’s Integrated Management of Childhood Illness singly and in combinations and vital status.Use of analytic methods to assess risk for mortality that complement (case-fatality and regression) and extend (machine learning) prior approaches.There may have been some variations in the assessments of clinical signs by the CHWs across study sites, although efforts were made to standardise them.

## Introduction

 Neonatal deaths comprise nearly half of all mortality in children before their fifth birthday.^1^ The most common causes of neonatal mortality, based on modelled estimates from global data, are complications of preterm birth (0.88 million, 36.0%); intrapartum-related events (‘birth asphyxia’) (0.58 million, 23.8%) and infections including pneumonia, sepsis and meningitis (0.4 million, 16.4%).^2^ Based on data from 11 surveillance sites in Africa and Asia, the Alliance for Maternal and Newborn Health Improvement (AMANHI) mortality study group found that perinatal asphyxia (40% in South Asia and 35% in sub-Saharan Africa) and severe infections (35% in South Asia and 37% in sub-Saharan Africa) were the most common causes of deaths in the neonatal period, followed by complications of preterm birth (19% in South Asia and 24% in sub-Saharan Africa).^3^ Similar results for rates and cause-specific mortality distributions were found in a 5-site, 3-country study in South Asia (Aetiology of Neonatal Infection in South Asia (ANISA)).^4^

Estimates of the incidence of severe neonatal infections have varied, but they nevertheless emphasise the magnitude of the burden. In 2012, a systematic literature review with meta-analysis estimated that the incidence of possible serious bacterial infection (PSBI) was 7.6%, totalling 6.9 million cases, with a case-fatality rate (CFR) of 9.8% in sub-Saharan Africa, South Asia and Latin America.^5^ A 6-country prospective study in 2010–2013 reported a 12.9% incidence of PSBI in the first 6 weeks after birth and a CFR of 14.0%.^6^

Recognising the need to provide guidelines on the identification and management of infections in young infants, based on several studies of clinical signs of illness associated with a need for hospitalisation of young infants during days 0 to <60,^7^,^13^ the WHO published Integrated Management of Childhood Illness (IMCI) in 2014, which included 7 signs of PSBI indicating the need for referral of sick young infants for hospital care.^14^ These signs were: not able to feed at all or not feeding well, convulsions, severe chest indrawing, high body temperature (38°C or above), low body temperature (less than 35.5°C), movement only when stimulated or no movement at all, or fast breathing (60 breaths per minute or more). In 2015, WHO further recommended outpatient treatment of infants aged 7–59 days who present with isolated fast breathing with oral amoxicillin without a referral,^15^ which was included in the 2019 IMCI chart booklet for young infants.^16^ WHO guidelines currently give equal importance to the other six PSBI signs. However, implementation of IMCI would be further aided by the identification of young infants with signs of illness at a lower risk for mortality who could potentially be treated on an outpatient basis. In addition, using mortality as the outcome in assessing the risk associated with signs of PSBI rather than the need for hospitalisation may enhance policy relevance.

We aimed to identify and pool individual subject data from studies globally that used similar methods to systematically assess infants for signs of PSBI, conducted by community-based frontline health workers, while also recording vital status during the young infant period. We will examine associations of signs individually and in combination with mortality to further define a level of risk for mortality and inform WHO IMCI global guidance for the assessment and management of young infants.

### Methods and analysis

#### Study populations

A literature review in consultation with WHO child health staff was conducted to identify population-based studies which assessed clinical signs of PSBI as defined by WHO^14^,^16^ and recorded the timing of deaths of young infants aged 0 to <60 days. We identified 6 studies which met these criteria, including the Simplified Antibiotic Treatment Trial (SATT) Pakistan,^17 18^ the African Neonatal Sepsis Trial (AFRINEST),^19^,^22^ Aetiology of Neonatal Infection in South Asia (ANISA),^23 24^ a community-based study in Pakistan,^25^ the Projahnmo-2 study in Bangladesh,^12 26 27^ and the National Institute of Child Health and Human Development (NICHD) Global Network’s Maternal and Newborn Health Registry study.^6^ The SATT Pakistan trial used community health workers (CHWs) to assess young infants for signs of PSBI in the community, but infants identified with signs were referred to health clinics and, if eligible, were enrolled in an antibiotic treatment trial and subsequently followed by nurses at the clinic.^18^ Since our study is aimed at assessing the risk of mortality associated with any sign of PSBI, alone or in combination, identified by CHWs and not physicians, and because data on CHW assessments across the entire young infant period were not available on infants enrolled in the SATT Pakistan study (as determined through discussion with the study principal investigators), this study was excluded. Zaidi *et al* evaluated young infants in Karachi, Pakistan, for PSBI identified using an algorithm-based approach that included signs overlapping with current IMCI signs of PSBI.^25^ Among infants identified with PSBI, families of infants who refused hospital admission were consented and enrolled in a three-arm community-based antibiotic treatment trial; however, because reporting on mortality outcomes was limited to these infants and was not population-based, this study was not included in our analysis. The NICHD Global Network’s Maternal and Newborn Health Registry study enrolled infants across seven rural sites in six countries who were assessed for the presence of various signs of serious infections and vital status over the first 6 weeks after birth. However, the variables in the site registries were not designed for the diagnosis of PSBI, and information for identifying infants with PSBI was not uniform across sites; thus, this study was excluded from our analysis.^6^

The two remaining studies (AFRINEST and ANISA) each used CHWs to conduct population-based surveillance to identify pregnancies, births and pregnancy outcomes and collected data through household visits on WHO signs of PSBI in young infants aged 0–59 days (tables1  2). Young infant clinical signs were assessed by similarly trained CHWs or community health extension workers (CHEWs, in the Nigeria site of AFRINEST) at the same time intervals over the first 60 days after birth. Home visits to assess young infants for signs of PSBI were an entry point into antibiotic treatment trials for the AFRINEST study^21 22^ or an observational study of infectious aetiology for ANISA.^24^ The management of infants with signs of PSBI differed across these studies—with randomisation of infants in the AFRINEST^21 22^ trials to various antibiotic treatment regimens, while ANISA^24^ focused on the identification of the aetiology of infection, and staff at the study sites managed infants according to local standard practice—which could have led to differential mortality risk across the studies. It is notable that the young infant mortality rate in the AFRINEST study (9.2 deaths in infants <60 days of age per 1000 live births)^28^ was substantially lower than the neonatal mortality rate for sub-Saharan Africa reported by AMANHI (20.1 per 1000 live births),^3^ which may reflect the treatment provided to infants in the AFRINEST study and may limit generalisability of the results of our analysis. ANISA confirmed young infant deaths and determined the cause of death using verbal autopsy, but AFRINEST did not.

**Table 1 T1:** Summary of studies to be included in pooled analysis of associations between clinical signs of PSBI and mortality of young infants in Africa and Asia

	AFRINEST^19^,^22^	ANISA^23 24^
Study design	Prospective, open-label equivalence RCTs	Prospective observational cohort study
Study years	2011–2013	2010–2015
Study sites	The DRC (Equateur province)Kenya (Busia, Bungoma and Kakamega counties in Western Kenya), Nigeria (Ibadan, Ile-Ife, Zaria)	India (Vellore, Odisha)Bangladesh (Sylhet)Pakistan (Karachi, Matiari)
Study aim	To evaluate simpler antibiotic regimens for the provision of safe and effective treatment of 0- to 59-day-old young infants with signs of clinically severe infection whose families do not accept or cannot access referral-level care. One trial had four arms and evaluated simplified antibiotic regimens for young infants with signs of clinical severe infections.^20^ Another trial had two arms and evaluated whether young infants with fast breathing alone can be safely and effectively treated in the community with oral antibiotics alone.^21^	(1) To establish community-based surveillance to identify cases of PSBI among infants aged 0–59 days and collect specimens for aetiological evaluation; (2) to determine community-acquired aetiology-specific incidence of bacterial and viral infections among infants by using standard and molecular diagnostic tools; (3) to identify the risk factors for community-acquired serious bacterial and viral infections in young infants and (4) to identify clinical features predictive of invasive viral and bacterial infections among ill-appearing young infants in the community.
Frontline health worker training	CHWs were used in DRC and Kenya; CHEWs were used in Nigeria.CHWs and CHEWs were trained by supervisory staff from the study sites. CHEWs had 2–3 years of formal training in government-supported training institutes on basic issues of maternal and child health, child nutrition, treatment of infections, immunisation and environmental health and oral and mental health. CHWs had been trained for a few weeks. Refresher training and standardisation exercises were conducted quarterly.	The study protocol was harmonised across sites, and project staff were trained similarly, using a two-stage training programme. In the first stage, experts from WHO trained the supervisory staff from the sites and provided them with training guides, videos and booklets. These trained personnel then trained CHWs from their respective sites for 15–21 days, with the length depending on the experience of the CHWs, local procedures and capacity. Refresher training was given ad hoc as CHWs were followed by a supervisor.
Pregnancy surveillance	Established a pregnancy surveillance system in all study sites. CHWs and TBAs identified and followed up on pregnancies in DRC and Kenya; TBAs and CHEWs identified and followed up on pregnancies in Nigeria.	CHWs identified MWRA and followed them via bi-monthly home visits to identify pregnancies based on the passage of >2 months since the last menstrual period.CHWs recorded the date of the last menstrual period, facilitated or encouraged accessing antenatal care, built rapport and arranged visits to assess newborn infants immediately after birth.
Birth surveillance	CHWs and TBAs identified births in DRC and Kenya, and TBAs and CHEWs identified births in Nigeria within 24 hours of delivery.	CHW followed up with pregnant women during two scheduled visits, immediately after identification of the pregnancy and at the 29th week of pregnancy. The CHWs provided their mobile phone numbers to family members and traditional birth attendants so that they could inform them about the delivery. The CHWs phoned the family every other day starting in the 37th week of pregnancy to enquire whether the mother had delivered.
Young infant inclusion criteria in PSBI surveillance	Liveborn infants in the study area who were visited at least twice by CHWs/CHEWs.	MWRA in the study area gave consent and gave birth to a liveborn infant that a CHW visited within 7 days of birth.
Young infant exclusion criteria in PSBI surveillance	Moved away for delivery or died before follow-up by CHWs/CHEWs after birth.	Infants born live to MWRA in the study area but were not reached by a CHW within 7 days of birth.
Baseline data collection	CHWs collected data using standardised questionnaires during pregnancy and home visits after childbirth. The first visit was as soon as the pregnancy was confirmed, and the second was 2 months before the expected delivery date. At the first home visit after the birth of liveborn infants, CHWs/CHEWs recorded pregnancy outcomes, date of birth, place of birth, birth attendant, postpartum status of the mother, participant demographics, home environment, birth weight, postpartum neonatal characteristics at birth, history of any complaints and examination of the baby to identify any signs of illness. CHW/CHEWs recorded maternal deaths, miscarriages, stillbirths and infant deaths in the first 2 months after birth.	CHWs collected data using standardised questionnaires during pregnancy and the first home visit of liveborn infants on participant demographics, home environment, pregnancy and birth history, postpartum maternal characteristics and neonatal characteristics at birth.
Clinical sign assessment (see table 2 for definitions of signs)	CHWs in DRC and Kenya and CHEWs in Nigeria visited infants at home on days 0, 2, 6, 13, 20, 27, 34, 41, 48 and 59. They identified sick young infants with PSBI signs and referred them to registered nurses at the health centres for further assessment and management. All infants continued to be assessed for all signs of PSBI at the community level by the CHWs and CHEWs, whether or not they were enrolled in a treatment trial.	CHWs made 10 scheduled home visits over the first 60 days after birth, ideally on days 0, 2, 6, 13, 20, 27, 34, 41, 48 and 59.
Management of infants	Infants identified with >1 sign of PSBI and enrolled in antibiotic treatment trials were managed according to trial protocols.^19^,^22^	Infants were managed according to standard care at the study sites.^23 24^ Blood and respiratory cultures were obtained from infants with signs of PSBI to identify the aetiology of infections.
Mortality assessment	The study outcome was the status of the child as alive or dead (all-cause) recorded by CHWs/CHEWs during home visits to assess infants for signs of PSBI.	CHWs assessed vital status at each home visit. Death cases were referred to supervisors of the verbal autopsy study, who conducted a verbal autopsy to determine the cause of death.
Young infants enrolled (N)	84 759 infants	63 017 infants
Young infant deaths (N)	587 deaths	1635 deaths

AFRINEST, African Neonatal Sepsis Trial; ANISA, Aetiology of Neonatal Infections in South Asia; CHEW, community health extension worker; CHW, community health worker; DRC, Democratic Republic of Congo; MWRA, married women of reproductive age; PSBI, possible serious bacterial infection; RCT, randomised controlled trial; TBA, traditional birth attendant.

**Table 2 T2:** Clinical signs of PSBI assessed in the studies included in pooled analysis

PSBI sign	AFRINEST	ANISA
Classification	Young infants in the community were assessed at each home visit by CHWs/CHEWs for all seven signs of PSBI.Young infants with signs of critical illness (inability to feed according to the mother, reported convulsions, no movement at all) were referred to a higher-level hospital for appropriate management. Those who refused referral to a hospital were treated with injectable antibiotics that day and advised for referral again on subsequent days. If they still did not accept the referral, they were treated with injectable antibiotics.Young infants with only fast breathing (infants aged 0–59 days with a respiratory rate >60 breaths per minute) were enrolled and randomised in the fast-breathing AFRINEST trial after the parents refused referral to a higher-level health facility/hospital for management and consented to be enrolled in the RCT.^20 21^Young infants with 1 or more of 5 signs of clinical severe infection (stopped feeding well (observed by a nurse at the health facility), high body temperature (axillary temperature >38°C), low body temperature (axillary temperature <35.5°C), severe chest indrawing and movement only on stimulation) were enrolled and randomised in the clinical severe infection AFRINEST trial after the parents refused referral to a higher-level health facility/hospital for management and consented to be enrolled in the RCT.^19 22^Young infants with signs of local infection (ie, pus in the umbilicus, skin or eye) were treated by a nurse at the health facility according to the WHO guidelines.	Any one sign of PSBI was defined as a case of PSBI.
Fast breathing	Respiratory rate >60 breaths per minute in 0- to <69-day-old infants	Respiratory rate ≥60 breaths per minute
Severe chest indrawing	Severe chest indrawing	Severe chest indrawing: Inward movement of the lower chest wall when the child breathes in
Fever	“High body temperature”: Axillary temperature >38.0°C	Axillary temperature ≥38°C
Hypothermia	“Low body temperature”: Axillary temperature <35.5°C	Axillary temperature <35.5°C
No movement	Movement only on stimulation or no movement at all	No movement or movement only on stimulation
Convulsions	Reported or observed convulsions	Convulsions (reported or observed)
Poor feeding	Stopped feeding well or unable to feed, according to the mother; confirmed by observation	The child is not able to feed at all or stopped feeding well (parental report and observed)

AFRINEST, African Neonatal Sepsis Trials; ANISA, Aetiology of Neonatal Infections in South Asia; CHEW, community health extension worker; CHW, community health worker; PSBI, possible serious bacterial infection; RCT, randomised controlled trial.

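### Table 2 prints different boundaries for fast breathing and fever in the two pooled studies, at odds with the Introduction, and the article states no common analysis definition

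*Protocol article*

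**What the plan says.** The Introduction lists the WHO signs with inclusive boundaries: "fast breathing (60 breaths per minute or more") and "high body temperature (38°C or above"). Study populations says the literature search looked for "population-based studies which assessed clinical signs of PSBI as defined by WHO".

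Table 2 then gives each study's definitions:

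- Fast breathing: AFRINEST "Respiratory rate >60 breaths per minute in 0- to <69-day-old infants"; ANISA "Respiratory rate ≥60 breaths per minute".
- Fever: AFRINEST "Axillary temperature >38.0°C"; ANISA "Axillary temperature ≥38°C".

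The Classification row of Table 2 repeats the strict AFRINEST boundary for fast breathing, "infants aged 0–59 days with a respiratory rate >60 breaths per minute", and again prints a strict boundary for high temperature.

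Exposures and outcomes takes the presence of any of the seven signs as the exposure. The case-fatality, Cox and machine learning sections all use each sign as a single yes/no variable. Study design says that individual data will be pooled with control for study and site. Analysis adds a sensitivity analysis of mortality risk by study and by site. The article states no common cut-off for the pooled signs. The limitation it acknowledges is variation in how health workers assessed signs, not a difference in definition.

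**The concern.** The pooled yes/no variable for fast breathing or fever should mean the same thing whichever study an infant comes from. As printed it does not. With no other sign, an infant at exactly 60 breaths per minute is exposed in ANISA and belongs to the no-sign reference group in AFRINEST. The same holds at exactly 38.0°C.

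The effect reaches other signs. The Cox analysis separates a sign found alone from the same sign found with another. An infant with severe chest indrawing and a rate of exactly 60 would count as chest indrawing alone in AFRINEST and as a combination in ANISA. Combinations are a central aim of the project, and the article names fast breathing in the first week as an example starting point for a decision app, so the meaning of this sign should be unambiguous.

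**Working it through.** **Step 1: set the definitions side by side.**

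| Sign | Introduction (WHO) | AFRINEST, Table 2 | ANISA, Table 2 |
|---|---|---|---|
| Fast breathing | ≥60 | >60 (printed twice) | ≥60 |
| Fever | ≥38°C | >38.0°C (and >38°C in the Classification row) | ≥38°C |
| Low temperature | <35.5°C | <35.5°C | <35.5°C |

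The low-temperature boundary agrees everywhere. The two signs with an inclusive boundary in the Introduction are the two that differ. The only readings classified differently are exactly 60 and exactly 38.0.

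**Step 2: what study adjustment covers.** From Table 1, crude deaths per 1000 infants are 587/84 759 × 1000 = 6.9 in AFRINEST and 1635/63 017 × 1000 = 25.9 in ANISA, a ratio of 25.9/6.9 = 3.7 (unrounded 3.75). Study populations cites 9.2 per 1000 live births for AFRINEST, which would give 25.9/9.2 = 2.8. Either way, study is strongly related to death, so control for study matters.

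**Step 3: illustration for a relative risk.** The inputs are assumptions, not figures from the document: relative risk R = 5 for rates above 60 against below 60, prevalence p = 5% for rates of 60 or more, a share h of those readings exactly at 60, and a relative risk b at exactly 60 anywhere from 1 to 5.

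- Inclusive definition: RR = h·b + (1 − h)·R. For h = 25% and b = 1: 0.25 + 3.75 = 4.00.
- Strict definition: RR = R ÷ {[(1 − p) + p·h·b] / [(1 − p) + p·h]}. For h = 25% and b = 5: 5 ÷ (1.0125/0.9625) = 4.75.

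| Share h at exactly 60 | RR, inclusive | RR, strict |
|---|---|---|
| 2% | 4.92–5.00 | 4.98–5.00 |
| 10% | 4.60–5.00 | 4.90–5.00 |
| 25% | 4.00–5.00 | 4.75–5.00 |

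**Step 4: crude against stratified.** Take the sign, as each study defines it, to have a relative risk of 5 in both studies, with prevalence 5% in ANISA and 5% × (1 − h) in AFRINEST, and overall risks from Table 1. The crude pooled relative risk is then 5.03, 5.17 or 5.46 for h = 2%, 10% or 25%. Stratified by study it is 5.00. Stratification removes this distortion, but not the difference in meaning shown in Step 3.

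**Step 5: case fatality, where no adjustment is stated.** Let f1 be the 7-day fatality above 60 and f0 that at exactly 60. The inclusive percentage is (1 − h)·f1 + h·f0. If f1 = 3% and f0 = 0.5% (assumed), h = 10% gives 2.7 + 0.05 = 2.75%, which is 8% below 3%. With h = 30% it is 2.1 + 0.15 = 2.25%, which is 25% below. If f0 = f1, the difference is zero for every h. These figures concern the ANISA percentage alone.

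**The case against.** The strongest reply is that Table 2 is misprinted. The studies were selected for using WHO definitions, and the AFRINEST column shows similar slips. Table 1 speaks of more than one sign for entry to the treatment trials, where Table 2 has one or more signs for one trial and fast breathing alone for the other. The fast-breathing cell gives an age limit of 69 days, while the Classification row gives 0–59 days. A lost inclusive symbol would explain the pattern. Against that, the strict symbol stands twice for each sign while the ANISA column prints the inclusive one, so the document cannot settle the question. This stands as real doubt about whether the studies differ, but either answer calls for a correction.

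A second reply is that study and site are controlled for and that results by study are planned. This also stands, as far as baseline risk goes. A reader might infer that the signs are confounded with study throughout. The plan does not support that for analyses that carry the stated control. What control cannot do is give one variable one meaning, and the case-fatality section states no adjustment. A by-study comparison would set the two definitions against each other.

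Third, the definitions part only at one value each. A reader might suppose that such readings are common because of rounding. The document does not say how rates or temperatures were recorded, so this is an assumption.

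Finally, an article condenses a fuller plan, and a harmonisation rule may exist there. All that can be said is that this article states none. The contradiction in the printed definitions does not rest on that silence.

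**Conclusion.** The point holds as an inconsistency in the exposure definitions, with a possible consequence for the analysis. The Introduction, the selection criterion and Table 2 cannot all be right as printed, and following Table 2 would classify boundary infants differently by study.

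The size is unknown. Under the assumptions above it ranges from nothing to a relative risk of 4.00 in place of 5.00 when a quarter of fast-breathing readings sit exactly on the boundary and carry no excess risk. With 2% on the boundary it is negligible. A reader might take the 8% to 25% fall in ANISA case fatality as an estimate of bias. It is not: both the share at the boundary and the low fatality there are assumed, and it describes no pooled or adjusted result. No comparable figure can be given for fever.

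This should be put right before the pooled variables are derived, but it does not undermine the pooled design. Which boundary is clinically right is not judged here.

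**What to change.** Reconcile the Introduction, the selection criterion in Study populations and Table 2, and state whether the two studies' cut-offs truly differ.

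- If the AFRINEST entries are misprints, correct Table 2, including the age limit in the fast-breathing cell. The cost is a text change.
- If the difference is real and numeric readings exist in both studies, derive each sign with one stated cut-off in both and run the other cut-off as a sensitivity analysis.
- If one study holds only yes/no, recode the study with numeric values to match it.
- If neither holds numeric values, report these two signs by study and state the difference as a limitation.

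No new data collection is needed. Recoding is cheap only if respiratory rates and temperatures were stored. The article speaks of extracting the presence of signs and does not say whether the readings are available, so that should be checked first. A count of readings at exactly 60 and exactly 38.0, where they exist, would show at once whether the issue is material.
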